### Statistical analysis

Baseline characteristics, including distributions of age, sex, ethnicity, and race, will be summarized as proportions, mean and standard deviation, or median and inter-quartile range as appropriate in the study population, with stratification according to whether the final adjudicated diagnosis was AMI.

The universal and sex-specific 99th percentile URLs derived from a separate reference range study (REF-TSIX) will be used to classify the Troponin T hs Gen 6 assay results, with values above indicative of a potential AMI [5]. Sensitivity, specificity, NPV, and PPV will be calculated using cTnT measurements taken at sample analysis times T0, T1, T3, T5, and T6 (Fig. 2), based on all evaluable samples available at each time point. Clinical performance measures will be reported with 95% confidence intervals (CIs) estimated using the Wilson score method [22]. The results will be shown for the total cohort as well as separately for females and males (determined by sex assigned at birth). A subpopulation excluding STEMI patients will also be analyzed.

Thresholds and delta change values for rapid algorithms (0/1 h and 0/2 h) to rule out and rule in AMI for evaluation in this study will be determined in a separate cohort, independent of this analysis. The results of the independent cohort analysis will be validated in this PERFORM-TSIX study cohort. Sensitivity, specificity, PPV, and NPV will be calculated with 95% CIs for the rule-out and rule-in criteria.

Risk prediction based on Troponin T hs Gen 6 strata and prognostic value for the classification of the algorithmic outcome categories (rule-out zone, observe zone, rule-in zone) will be analyzed with respect to short-term (30-day) and long-term (180-day) outcomes (MACE [MI (including type of MI for the 30-day follow-up), all-cause death (cardiac and non-cardiac) [21]). The Kaplan–Meier method will be used to perform time-to-event analysis to compare the survival probabilities for different TnT strata and algorithmic outcome categories (rule-out zone, observe zone, rule-in zone). To this end, hazard ratios calculated from the Cox regression model and cumulative event-free rates will be reported to quantify the difference in risk between groups.

To determine the clinical performance of the Troponin T hs Gen 6 assay measured 3 h following presentation to the ED (primary objective), the sensitivity for a CEC-adjudicated diagnosis of AMI will be calculated at the sex-specific and universal 99th percentile URL. Assuming an expected sensitivity of 90%, and setting the two-sided significance level of 5%, a sample size of at least 160 patients with AMI is required to give power of at least 80% [23], using a statistical test based on an acceptance criterion of 81% for the LCL for sensitivity.

To validate the clinical performance of the Troponin T hs Gen 6 assay in a 0/1 h algorithm (secondary objective), an NPV of greater than 99% was expected for those patients stratified as rule out [8]. To provide at least 80% power at 5% significance, 1356 patients were required who met the criteria for rule out, using a statistical test based on the acceptance criterion of 98% for the lower bound of the 95% CI for the NPV. Assuming approximately 60% of patients met the criteria for rule out [4, 24], a total sample size of 2326 evaluable patients with samples at 0 and 1 h was required. Such a total sample size enabled the certainty of 95% that 1356 patients who met the criteria for rule out would be found in a sample of 2326 patients (Schaetzkin adjustment) [25], given the assumptions mentioned above. Based on a minimum sample size of 2326 patients and accounting for incomplete sample collection for T0/T1 samples of around 35% [23], a 10% dropout rate, as well as regional representation due to regulatory requirements, we aimed to recruit approximately 5600 patients.

All cTn results will be stored in a Web-based Computer Aided Evaluation (WebCAEv) database. For statistical analysis, the data from WebCAEv and the eCRF will be exported and merged using the statistics software R [26].

## Discussion

The PERFORM–TSIX study aims to evaluate the clinical performance of the Troponin T hs Gen 6 assay as an aid in the diagnosis of AMI in a prospective, multinational real-world cohort. Clearly defined acceptance thresholds and the use of diagnostic, algorithmic validation, and prognostic endpoints will ensure the study results are relevant for clinical practice. The patient enrollment using broad inclusion criteria and geographically diverse sites will reflect the real-world use of cTn assays. The inclusion criteria include secondary symptoms of AMI, which are more prevalent in numerous subcohorts, including elderly patients and patients with diabetes [27, 28]. While female and male patients are as likely to present with chest pain, female patients are more likely to report additional symptoms [29–31]. The inclusion of symptoms other than chest pain should ensure that the results are relevant to the broad range of patients who undergo evaluation for suspected ACS. In addition, the adjudicated final diagnosis is based on all available clinical data, irrespective of the number of cTn time points available.

The global population, large sample size, and representation from different healthcare settings, including community hospitals and tertiary care centers, as well as liberal inclusion criteria, will enhance the real-world applicability of the study results. Notably, previous studies evaluating the performance of hs-cTn assays have tended to be performed in smaller populations enrolled from a single healthcare system or country [3, 32–36]. The large sample size will also allow for secondary analyses, while the inclusion of patients from different racial and ethnic groups will enable the study to account for potential variations in cTn levels based on race and ethnicity [37, 38].

Validation of the Troponin T hs Gen 6 assay for use in rapid rule-in and rule-out algorithms is an added benefit of the study design and will allow the assessment of the assay performance in guideline-recommended clinical pathways. In a meta-analysis of 30,066 patients, the 0/1- and 0/2-h algorithms demonstrated a higher sensitivity and NPV than a 0/3-h algorithm using the 99th percentile to rule in and rule out AMI [39]. Additionally, it has been shown that the ESC 0/1-h algorithm allows earlier clinical decision-making, which can reduce the total time to discharge by reducing the length of stay in the ED [3, 7, 39, 40]. Validating the performance of the new assay in these rapid algorithms will help to support effective implementation of the Troponin T hs Gen 6 assay.

In addition to diagnosing AMI when a patient presents to the ED, cTn may be beneficial for the prognosis of other cardiovascular diseases [41–43]. As well as determining the diagnostic use of the Troponin T hs Gen 6 assay, the PERFORM-TSIX study will evaluate the assay’s utility for risk stratification and prediction of subsequent death and MACE at 30 and 180 days.

Our study is not without limitations. First, while a global study provides a robust evaluation of overall assay performance, because no single population is solely represented, application of the overall results to any specific locality may require subset analysis for the best accuracy. It is also possible that local or regional standards of care or practice protocols at individual hospitals influenced sample collection procedures and the availability of samples at some time points. In addition, as with any prospective investigation, patients may be lost to follow-up; however, the large sample size and robust follow-up methods (e.g., second telephone number, checking hospital records, multiple phone calls, and sending a letter to the patient’s address) will improve follow-up completion and reduce the risk of selection bias. Furthermore, patients who missed any of the predefined sample collection time points were excluded from the analysis at that time point, reducing the number of samples available for analysis and providing undefined bias. However, it might be noted that patients missing later follow-up time points are likely to be lower-risk patients (i.e., those with early or rapid discharge) and the exclusion of these patients is unlikely to have a significant influence on our outcomes. Those patients still received an adjudicated diagnosis.

As our study included an all-comers population, it is possible that patients may have been enrolled late after the onset of symptoms; therefore, a subanalysis based on early versus late presenters according to symptom onset (rather than presentation to the ED) may be beneficial. In addition, the all-comers population will result in the inclusion of patients with STEMI, which may bias the performance of a cTn assay as patients with STEMI show higher cTn levels compared with patients with NSTEMI [44]. Despite higher cTn concentrations in STEMI overall, a high proportion of patients with STEMI have low or undetectable cTn concentrations at presentation due to both early presentation as well as abrupt coronary occlusion that may initially prevent cTn release into the circulation [45], which could lead to false-negative results. cTn is not the recommended way to diagnose STEMI in the ED, where time is of the essence and the ECG and clinical presentation alone are typically used. However, patients with STEMI should not be actively excluded in trials evaluating cTn assays, as ST elevations may be unclear in the initial ECG and in such settings, cTn can be important to confirm a diagnosis of AMI. To overcome this potential bias, a subanalysis excluding STEMI patients will also be performed.

Finally, as cTn is integral to the diagnosis of AMI, there is a risk of confirmation bias, but this is integral to all diagnostic performance studies evaluating novel cTn assays. It may be speculated that if a different hs-cTn assay were used as the gold standard, the data to support clinical performance may vary. However, an effort has been made to minimize this by using an independent CEC to perform diagnostic adjudication using standardized criteria, including rules about what to do when some of the clinical and/or biochemical information was missing, whilst blinded to the results of the Troponin T hs Gen 6 assay.

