### Outcomes

The primary diagnostic outcome measure is the sensitivity of the Troponin T hs Gen 6 assay for a clinical events committee (CEC)–adjudicated diagnosis of AMI when measured 3 h post-ED presentation (defined as samples collected 121 to 240 min post-ED presentation). Patients are only eligible for inclusion in the evaluation of the primary diagnostic outcome if at least one blood sample was collected within the defined timeframe of 121 to 240 min post-ED presentation. If more than one sample was collected within the window, the sample closest to the middle of the window will be used. Acceptance criterion for the primary endpoint is 81% for the lower confidence limit (LCL) for sensitivity.

Secondary outcome measures for the clinical performance of the Troponin T hs Gen 6 assay at additional time points are sensitivity, specificity, negative predictive value (NPV), and positive predictive value (PPV); measures to validate the thresholds for a 0/1-h algorithm to rule out AMI include sensitivity, specificity, NPV, and PPV. Acceptance criterion for the 0/1-h algorithm to rule out AMI is 98% for the LCL for NPV.

Exploratory outcome measures to validate the thresholds for a 0/1-h algorithm to rule in AMI and a 0/2-h algorithm to rule in and rule out AMI include sensitivity, specificity, NPV, and PPV.

To evaluate the prognostic value of the Troponin T hs Gen 6 assay, risk prediction for major adverse cardiovascular events (MACE) at 30 and 180 days will be analyzed for the different algorithmic outcome categories (rule-out, observe, rule-in).

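### Excluding early-discharged patients is called harmless for all outcomes, but that reasoning covers at most sensitivity; specificity and NPV at 3, 5 and 6 h would be biased downward

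*Protocol article*

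**What the plan says.** The Statistical analysis section computes sensitivity, specificity, NPV and PPV at T0, T1, T3, T5 and T6, "based on all evaluable samples available at each time point". The Outcomes section applies the same rule to the primary endpoint: "Patients are only eligible for inclusion in the evaluation of the primary diagnostic outcome if at least one blood sample was collected within the defined" window of 121 to 240 min.

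The limitations paragraph of the Discussion confirms that "patients who missed any of the predefined sample collection time points were excluded from the analysis at that time point", and describes the consequence as "reducing the number of samples available for analysis and providing undefined bias". It then argues that "patients missing later follow-up time points are likely to be lower-risk patients (i.e., those with early or rapid discharge" and concludes that "the exclusion of these patients is unlikely to have a significant influence on our outcomes". It adds: "Those patients still received an adjudicated diagnosis".

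The conclusion is not limited to sensitivity. The article's outcome measures at these times also include specificity, NPV and PPV.

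**The concern.** The reason given for reassurance is itself a reason to expect bias. If the chance of having a later sample depends on risk, patients with the sample are not a random subset of those enrolled. Patients sent home early because they look low-risk are mainly people without AMI and with troponin below the 99th percentile, which makes them true negatives. Specificity and NPV both count true negatives; sensitivity does not.

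At stake is how the later specificity and NPV are read. The article presents the study as an all-comers cohort with real-world applicability. A reader who accepts the reassurance would take the 3, 5 and 6 h values as describing that cohort, when they describe the patients still being sampled at those times.

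**Working it through.** **The plan's own figures.** The article gives no figure for the size of this bias, so there is none to reproduce. Its one sampling-loss figure is "incomplete sample collection for T0/T1 samples of around 35" per cent, which concerns the 0 and 1 h samples. It is used only to inflate numbers: 2326 / 0.65 / 0.90 ≈ 3976, with the rest of the approximately 5600 attributed to regional representation. The inflation replaces lost numbers. It does not address who is lost.

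**Inputs.**
- From the article: the exclusion rule, the account of who is missing, and an expected sensitivity of 90%.
- Assumed, because the article does not give them: AMI prevalence 5–15%, full-cohort specificity 80–90%, and 35% of the cohort missing (the 0/1 h figure, borrowed for later times).

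**Formulas.** Sensitivity = TP/(TP+FN). Specificity = TN/(TN+FP). NPV = TN/(TN+FN). PPV = TP/(TP+FP). TN appears only in specificity and NPV.

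**Worked case, per 1000 patients, 10% AMI, specificity 90%.** Full cohort: TP 90, FN 10, TN 810, FP 90. Remove 350 patients, all true negatives, leaving TN 460.
- Sensitivity: 90/100 = 90.0%, unchanged.
- Specificity: 810/900 = 90.0% becomes 460/550 = 83.6%.
- NPV: 810/820 = 98.8% becomes 460/470 = 97.9%.
- PPV: 90/180 = 50.0%, unchanged.

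**Across the assumed range (35% missing, all true negatives).**

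| AMI | Specificity, full → analysed | NPV, full → analysed |
|---|---|---|
| 5% | 80.0 → 68.3 | 99.35 → 98.80 |
| 5% | 90.0 → 84.2 | 99.42 → 99.02 |
| 10% | 80.0 → 67.3 | 98.63 → 97.37 |
| 10% | 90.0 → 83.6 | 98.78 → 97.87 |
| 15% | 80.0 → 66.0 | 97.84 → 95.65 |
| 15% | 90.0 → 83.0 | 98.08 → 96.51 |

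Specificity falls by 5.8 to 14.0 points and NPV by 0.40 to 2.19 points.

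**Other mechanisms (10% AMI, specificity 90%).**
- Only 15% missing, all true negatives (TN 660): specificity 660/750 = 88.0%, NPV 660/670 = 98.5%, PPV unchanged.
- Mixed loss of 40% of TN, 10% of FP and 5% of AMI patients (TN 486, FP 81, TP 85.5, FN 9.5): specificity 85.7%, NPV 98.1%, PPV 51.4%.
- Loss depending on AMI status only, 350 non-AMI patients removed in proportion (TN 495, FP 55): specificity stays 90.0%, NPV 495/505 = 98.0%, PPV 90/145 = 62.1%.
- Loss completely at random: nothing changes.

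NPV falls under every risk-related mechanism above. Specificity falls when, among non-AMI patients, those below the limit are lost more often than those above it, as early discharge of low-risk patients implies.

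**The case against.** The best defence has four parts.

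- **The bias is disclosed.** The same paragraph concedes a bias and notes that local practice may affect sample availability. This stands. The fault is the unqualified dismissal that follows.
- **The target is legitimate.** Performance among patients who have a sample in the window is a proper estimand, and the Outcomes section defines the primary analysis that way. This also stands, but that subset then has to be named as the target. It does not show that exclusion leaves the all-comers results unaffected.
- **The direction is unfavourable to the assay.** Losing true negatives lowers specificity and NPV, so it does not flatter the product. True, but a downward bias is still a bias.
- **Sensitivity analyses belong in a SAP.** The SAP is not shown and may contain them, so their absence from the article is not the finding. The over-broad statement is in the article.

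A reader might infer more than the documents support:

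- **That PPV is biased too.** Losing true negatives alone cannot change it. It moves only if false or true positives are lost selectively.
- **That the primary endpoint is compromised.** This would need selective loss of AMI patients. For example, losing 30% of false negatives and no true positives would move sensitivity from 90% to 0.90/(0.90 + 0.10 × 0.70) = 92.8%. Nothing in the article says that this happens, and it gives no missing share for AMI patients at 3 h, so worst-case bounds would rest on invented inputs.
- **That STEMI patients leave before later draws.** The Discussion's remark on urgency concerns ECG-based diagnosis, not missed samples, and an analysis excluding STEMI is already planned.
- **That the 0/1-h NPV criterion is undermined.** The disputed sentence concerns later time points, so the link is indirect.
- **That a trend in accuracy over time is distorted.** No stated objective compares accuracy between time points.

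**Conclusion.** The point holds in limited form. The reassurance is sound for sensitivity as far as the excluded patients do not have AMI. By the article's own account of who is missing, it does not hold for specificity and NPV at 3, 5 and 6 h, which are biased downward relative to the enrolled cohort.

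The real size is unknown. The 6–14 points for specificity and 0.4–2.2 points for NPV rest on the assumed prevalence and specificity, a missing share borrowed from the 0/1 h figure, and the extreme case that every missing patient is a true negative. A smaller or more mixed loss gives smaller shifts. This is worth correcting, but it does not threaten the primary conclusion.

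**What to change.** 1. Limit the reassurance to sensitivity, with its condition that those lost are non-AMI patients. State that specificity and NPV at the later times are expected to be lower than in the full cohort, and that PPV may shift if positives are also lost selectively.
2. For each window, report baseline characteristics and the adjudicated AMI rate for patients with and without a sample.
3. Unless the SAP already provides it, add a sensitivity analysis weighted by the inverse probability of having a sample in the window, beside the complete-case results. The adjudicated diagnosis and baseline data needed are already held.

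The weights should not rest on AMI status alone. In the worked case, scaling the 550 remaining non-AMI patients back to 900 gives TN 460 × 900/550 = 752.7 and FP 147.3. NPV then recovers to 752.7/762.7 = 98.7%, but specificity stays at 83.6%. The model therefore also needs baseline variables that predict a low result.

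Classifying AMI patients without a 3 h sample by their last earlier value should not be offered as a conservative bound. The article defines AMI by a rise and/or fall, and an earlier value may be the higher one.

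Cost: text changes and additional analysis of existing data. The downside is a missingness model that must be stated and defended, and slightly wider intervals.

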## Conclusion

PERFORM-TSIX is a prospective, international, observational, multicenter, longitudinal cohort study evaluating the clinical performance of the Troponin T hs Gen 6 assay as an aid in the diagnosis of AMI. The study will also determine the assay’s performance to rule in or rule out AMI using rapid algorithms and to risk-stratify patients for short- and long-term outcomes. The main strengths of the study are the large sample size, diverse global population, and inclusion of healthcare centers with different levels of care, which will ensure the findings can be applied in many populations and settings.

